### **5.2.3 DTH Placement and Biopsy Procedure**

After completing RT and along with vaccination #1 patients will undergo baseline DTH testing with standard recall antigens. The vaccine site will also be assessed for a DTH-type response. Recall antigens (Tetanus toxoid, *Candida*, and *Trichophyton*) will be prepared and administered according to SOP-JHS-HDC-CL-014 “Delayed type hypersensitivity testing and biopsy procedure”. Beginning at the time of the fourth vaccination, the DTH tests for recall antigens will be repeated. An additional leukapheresis will be required for any patients who have a positive DTH skin test for PEPvIII for immunologic monitoring. The patient will be monitored after the administration of all skin tests for the development of severe allergic reactions. A physician or nurse who has completed an ACLS course will supervise the skin tests, and a cardiac resuscitation cart will be available in the immediate vicinity when performing these procedures. A 5 mm diameter of erythema or induration will be considered positive. Patients with positive reactions at the site of human PEPvIII-KLH will be biopsied under local anesthesia for evaluation of the infiltrate (SOP-JHS-014 “Delayed Type Hypersensitivity Testing and Biopsy Procedure”). The biopsy will be a standard 4 mm “punch” biopsy routinely used in the Dermatology Clinic.

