### **8.1.1 Overview of Statistical Analysis**

Our laboratory and the HVTN Immunologic Monitoring Reference Laboratory, headed by [name] also at Duke University, has devoted considerable effort to co-developing and co-validating the immunologic assays outlined below for monitoring  $T_{Reg}$  function, antigen-specific responses in CD8+ or CD4+ T-cells, and NK cell functional activity in cancer patients. The reproducibility of these assays in our hands ensures that they can be reliably used for monitoring of changes after vaccination with and without daclizumab. Power calculations for this study are based on our primary endpoint which is functional suppressive capacity of CD4+CD25+CD127-  $T_{Regs}$ . For these calculations, we assumed that measurements made in each treatment group at a given phytohemagglutinin (PHA) level would be normally distributed with standard deviation of  $\sigma$ . Based on our experience with these assays within this patient population (Fecci, Mitchell et al. 2006), we estimate that with a sample size of 20 randomized patients we will have 80% power to detect a difference of 1.41  $\sigma$  at the 0.017 significance level (one-tailed). A 0.017 level of significance is used to adjust (Bonferroni correction) for the use of 3 non-zero PHA doses (0.1, 1, 10  $\mu$ g/well) in the proliferation assay. Thus, with only 20 patients, we will have sufficient power to detect treatment effects much more subtle than the ones observed in our pre-clinical studies (Fecci, Sweeney et al. 2006) and effects that we believe would be clinically significant. However, because the magnitude and variability of the effects of daclizumab on  $T_{Regs}$  remain unknown in humans, once human data become available from these studies, power analyses will be recalculated and patient numbers adjusted if needed. If daclizumab treatment does not significantly inhibit the functional recovery of  $T_{Regs}$  (primary endpoint), we would not be interested in the further development of this drug as

a vaccine adjuvant. Therefore, a one-sided hypothesis test is utilized. Power calculations are not provided for subsequent analyses as the number of patients in this trial will be determined by the primary endpoint, and the remainder of the analyses is exploratory and hypothesis generating only. With 10 patients in each arm, however, we will have 80% power to detect difference  $>1.325\sigma$  between groups for each assay at  $\alpha=0.05$ .

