
### **8.2.1 Statistical Analysis**

Our primary endpoint analysis will consist of a comparison of proliferative T-cell response to PHA among treatment groups (+/- daclizumab) using a generalized linear model for normal data that accounts for correlation of measurement replication across PHA doses (0, 0.1, 1, 10  $\mu\text{g/well}$ ) within subjects. This analysis determines whether the difference in treatment groups relative to proliferative response remains constant over 4 PHA doses (i.e. curves remain parallel or not). A test of interaction with 3 degrees of freedom will be used. If the curves deviate significantly from parallelism, we will conclude that the effect of treatment varies as a function of PHA dose level. Within the

context of this model, statistical contrasts will be used to assess treatment differences at specific PHA dose levels. If the test for interaction is not statistically significant, one will conclude that the treatment effect is constant over PHA dose levels. A generalized linear model without an interaction will be used to assess whether the main effect for treatment is statistically significant (i.e. treatment differences are non-zero). In this analysis and others, if assumptions required for t-tests are not satisfied, a non-parametric Wilcoxon rank sum test will be conducted at each PHA level. Significance for this and other assays will be taken at the  $\alpha=0.05$  level unless otherwise indicated. A Bonferroni correction will be used to control for the multiple comparisons.

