#### **8.4.1 Statistical Analysis**

A two-sided t-test will be used to compare cytokine differences between treatment groups as described above.

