### **8.7.1 Statistical Analysis**

Assuming that all patients will have no response before vaccination, each patient will be classified as a responder or non-responder based upon an induration at the response site  $\geq 10$  mm. Fisher's exact test will be used to compare responses between groups after each vaccination.

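### The 80% power stated for every assay is a t-test figure and does not apply to DTH, which is cut at 10 mm and compared by Fisher's exact test

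*Protocol*

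**What the plan says.** Protocol 8.1.1 first says that power is not calculated for the non-primary analyses, which are exploratory. It then adds: "With 10 patients in each arm, however, we will have 80% power to detect difference" above 1.325 sigma "between groups for each assay at" alpha = 0.05. No assay is excepted.

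Protocol 8.7.1 sets the DTH analysis: "each patient will be classified as a responder or non-responder based upon an induration at the response site" of 10 mm or more, and "Fisher's exact test will be used to compare responses between groups after each vaccination". No responder rates, no separate power and no analysis of the diameter itself are given.

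Protocol 5.2.3 defines a positive skin test differently: "A 5 mm diameter of erythema or induration will be considered positive".

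On timing, 8.7 and 6.2.4 place the post-baseline test at the fourth vaccination. The flow sheet also appears to mark a DTH test at immunization #3 and at progression. No section schedules one after every vaccination, as 8.7.1 implies.

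**The concern.** A difference in sigma units has meaning only for a measurement kept on its continuous scale. DTH is read as a diameter, but 8.7.1 turns it into a yes/no before the only between-arm test. That discards information, and at 10 against 10 Fisher's test is also very conservative. A reader who takes 8.1.1 at its word would treat a null DTH comparison as having had an 80% chance of finding a large effect, and it did not.

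The result also depends on where the cut falls, and the protocol has two. A 7 mm induration is positive under 5.2.3 and a non-response under 8.7.1.

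**Working it through.** **Inputs.** From 8.1.1: n = 10 per arm, difference d = 1.325 sigma, alpha = 0.05, stated power 80%. The 0.05 level is repeated in 8.2.1 ("Significance for this and other assays will be taken at the" 0.05 level). Sidedness is not stated for DTH; 8.4.1 makes the cytokine t-tests two-sided. Responder rates at the 10 mm cut and the SD of induration are not given, so the control rate is varied.

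**Step 1: reproduce the stated figure.** Two-sample t-test, df = 18, noncentrality d × √(n/2) = 1.325 × √5 = 2.963. Two-sided power at 0.05 is 0.800. A one-sided t-test gives 0.886 and a two-sided normal approximation 0.842. So the claim is a two-sided t-test on a continuous value.

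**Step 2: the same shift, analysed as 8.7.1 plans.** Assume normal induration with equal SD. If a proportion p0 of controls passes the cut, then p1 = 1 − Φ(Φ⁻¹(1 − p0) − 1.325) of the daclizumab arm does. Power is the sum of Bin(i; 10, p0) × Bin(j; 10, p1) over all tables (i, j) with two-sided Fisher p ≤ 0.05. For example, 2 control responders need at least 8 in the other arm.

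| Control responders | Daclizumab responders | Fisher power |
|---|---|---|
| 10% | 51.7% | 32.4% |
| 20% | 68.6% | 39.8% |
| 25.4% | 74.6% | 40.6% (maximum) |
| 30% | 78.8% | 40.1% |
| 40% | 85.8% | 36.7% |
| 50% | 90.7% | 31.2% |
| 70% | 96.8% | 11.1% |

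On the same normal data a Wilcoxon rank sum test on the millimetres has 75.9% power (20,000 simulations). Over the tabulated rates the loss is:
- against the t-test: 80.0 − 40.6 = 39 points to 80.0 − 11.1 = 69 points;
- against Wilcoxon: 75.9 − 40.6 = 35 points to 75.9 − 11.1 = 65 points.

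Part of the loss is Fisher's conservatism: its actual two-sided size at 10 per arm never exceeds about 0.013. Under this model, with the cut and Fisher kept, 80% would need about 18 per arm at the best cut (power 0.82) or a difference of about 2.0 sigma at 10 per arm (0.80).

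**Step 3: zero-heavy induration.** Assume non-responders read 0 mm and responders average 18 mm (SD 4), all of them counted as passing the cut. Group variance is p × 4² + p(1 − p) × 18².
- 20% v 75% responders: variances 55.04 and 72.75, pooled SD 7.99, difference 0.55 × 18 = 9.9 mm, or 1.24 sigma. Fisher 53%, Wilcoxon 64%, t-test 70%.
- 20% v 80% responders: variances 55.04 and 64.64, pooled SD 7.74, difference 0.60 × 18 = 10.8 mm, or 1.40 sigma. Fisher 64%, Wilcoxon 72%, t-test about 79%.

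These two cases bracket 1.325 sigma. Fisher loses about 8 to 11 points to Wilcoxon and remains below 80%.

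**The case against.** **The power sentence was never meant for DTH.** It follows a statement that the remaining analyses are exploratory and not separately powered; 8.1.1 introduces assays of T-reg function, antigen-specific T cells and NK activity, not skin tests; and sigma units can refer only to continuous readouts. This fairly lowers the stakes. It does not make the sentence right, because its wording covers each assay and excepts none.

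**The normal model is wrong for skin tests.** This has force. Section 8.7.1 itself assumes no response before vaccination, and 3.4.3 reports the earlier vaccine trial as having no DTH response at baseline and 62% of patients reactive at 6 months. Such data are closer to Step 3, where the loss is much smaller. A reader might infer from Step 2 that about 41% is a ceiling on the DTH power. It is not: it holds for two-sided Fisher under normality and equal SD. One-sided Fisher reaches 60% under the same model, though a one-sided reading does not reproduce the protocol's 80%.

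**A responder endpoint is customary.** Reporting responder proportions is reasonable. The difficulty is making them the only between-arm test when the diameters are already measured.

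**DTH decides little.** Largely true. The recall antigens in 8.7 gauge general immunocompetence. Only the vaccine-site reading in 5.2.3 bears on responses induced by CDX-110, the subject of the second secondary objective. Section 8.1.1 ties further development of daclizumab to the primary endpoint.

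**Conclusion.** The concern holds in a limited form. The 80% in 8.1.1 is correct for a two-sided t-test and wrong for DTH as analysed in 8.7.1. Planned power is 11% to 41% under the normal, equal-SD model for control responder rates of 10% to 70%, and about 53% to 64% in the zero-heavy cases at 1.24 to 1.40 sigma. The rank test on millimetres did better in every scenario checked, by roughly 8 to 11 points in the zero-heavy cases and 35 to 65 in the normal ones. These sizes rest on assumed distributions, since the protocol gives none for induration.

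A reader might also infer that the trial is undersized or that a secondary objective fails with this test. The documents do not support either: the sample size comes from the primary endpoint, and DTH is one exploratory readout among several. The 5 mm and 10 mm definitions conflict as written and must be reconciled; the documents do not show which one the analysis should use.

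**What to change.** - **8.7.1:** compare induration in millimetres between arms, separately for each antigen, with a Wilcoxon rank sum test at the scheduled vaccination-4 test. For recall antigens, use the pre-vaccination reading already collected, as change from baseline or by baseline adjustment, instead of assuming no prior response. Report responder proportions descriptively. Replace the comparison after each vaccination with the visits at which skin tests are actually done, and bring the flow sheet into line.
- **5.2.3 and 8.7.1:** reconcile the two definitions of a positive response, or say why they differ.
- **8.1.1:** restrict the 80% statement to assays analysed on a continuous scale by t-test. It would then also stop covering the rank and Fisher comparisons in 8.5.1 and the chi-squared test in 8.11.1.

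The cost is wording. The diameter must be measured to apply either cut, so no visits, samples or patients are added.

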## **8.8 PBMC Proliferation and Cytokine Secretion ELISA**

Peripheral blood will be used to test antigen induced T-cell proliferation before each immunization. PBMC will be stimulated with PEPvIII peptide, KLH, a control peptide mix, (*HIV* pol), Tetanus, and the non-specific mitogens PHA and Con-A. The plates will be incubated at 37°C for 5 days. Proliferation will be measured by counting the incorporation of  $^3\text{H}$ -thymidine in dividing cells. For detection of cytokine secretion, 1 mL cultures will be set up in 24 well plates using  $5 \times 10^5$  T-cells stimulated with PEPvIII-KLH. At the end of a 5-day incubation at 37°C the supernatant from the cultures will be removed, filtered and assayed for the presence of the cytokines IFN- $\gamma$ , IL-2, IL-4 IL-5, TNF- $\alpha$  and IL-10, IL-12, IL-13, GM-CSF to determine the Th1/Th2 profile by BIO-Plex Cytokine Reagent Kit (171-30400, BIO-Rad, Hercules, CA 94547).

### **8.8.1 Statistical Analysis**

All data will be background subtracted and compared using two-sided t-tests as described above.

## **8.9 Serology**

Quantitative anti-EGFRvIII extracellular domain, PEPvIII, and KLH antibody concentration in the serum will be measured by FACS analysis of antigen-coated magnetic beads (Dyna-MIAT - Magnetic Immobilized Antigen Technique) in our laboratory. Briefly, antibody levels to specific antigens will be determined by FACS analysis of antigen immobilized beads as described in preliminary data section. Beads are reacted with serum, washed, and developed with fluorochrome conjugated polyclonal anti-human secondary. Antigens used in this assay will include EGFRvIII extracellular domain, PEPvIII, and KLH, CEF peptide mix, total tumor lysate, and autologous normal brain lysate. Bead performance is validated by comparing serum reactivity of antigen-specific beads to serum reactivity with antigen transfected cells. As another means of verification, sample serums will be pre-incubated with excess specific and non-specific antigens, insuring that human antibody binding is specific.

### **8.9.1 Statistical Analysis**

All data will be background subtracted and compared using two-sided t-tests as described above.

## **8.10 NK Cell Assays**

After gradient centrifugation, the lymphocyte population is identified based on characteristic forward and side scatter patterns, NK cells then are counted, sorted, (or isolated (NK Cell Isolation Kit II (negative selection), MACS, Miltenyi Biotec)) based on being CD3 and CD56+ (BD Pharmingen) using a FACS Aria. CD56bright cells are further differentiated by being CX3CR1 (MBL International)(Li, Lim et al. 2005). For cytokine analysis, purified populations (>95%) are placed in RPMI 1640 media with FCS and left unstimulated or stimulated with IL-12 (20 ng/mL) and IL-15 (100 ng/mL) (PeproTech) for 72 hours. Supernatants are analyzed by a Luminex 100 machine (Luminex Corporation, Austin, Texas) as described above.

To evaluate for the effects of NK cells on CD4+ and CD8+ T-cell proliferation overall and in an antigen-specific manner, PBMCs at baseline and after daclizumab therapy *in vivo* will be obtained from peripheral blood, cultured in X-VIVO 15 media ((Bio Whittaker) labeled with CFSE (Molecular Probes, 1μM), and activated either polyclonally with plate bound CD3 (20 ng/mL, OKT3 #16-0037) / CD28 (10μg/mL, CD28.2 #16-0289) (eBioscience) or with the specific antigen PEPvIII-KLH, or normal brain or tumor homogenate for 72 hours in the presence or absence of daclizumab (matched for sample). For half the samples, NK cells will be removed with CD56 beads (Miltenyi Biotec). The samples are then washed and re-seeded in media with IL-7 and IL-15. The numbers of T cells and NK cells is analyzed as described above.

The effect of daclizumab therapy on the cytotoxicity of NK cells against resting or activated T-cells will be tested using standard Cr release assays. T-cells (T cell Isolation Kit II, MACS, Miltenyi Biotec) and NK cells (NK Cell Isolation Kit II (negative selection), MACS, Miltenyi Biotec) will be isolated and mixed at various effector:target ratios after labeling T-cells with Cr overnight. For certain assay subsets CD56bright cells are further differentiated by being CX3CR1 (MBL International)(Li, Lim et al. 2005) using a FACS Aria as described above. After 4 hours, at 37° and 5% CO2, supernatants are harvested and counted. Data is analyzed with the spontaneous release subtracted.

### **8.10.1 Statistical Analysis**

All analyses will be conducted as described above for T-cells.

## **8.11 Sub-clinical Autoimmunity**

Patients will also be assessed before vaccine #1 and every 4 months after vaccine # 3 by a panel of clinical laboratory analyses to screen for the development of autoimmunity. The most common manifestations of autoimmunity seen in related trials(Phan, Yang et al. 2003; Attia, Phan et al. 2005; Blansfield, Beck et al. 2005; Jaber, Cowen et al. 2006) have included enterocolitis, dermatitis, uveitis, hepatitis, and hypophysitis. Laboratory evaluations to detect subclinical disease will be obtained as follows: serum thyroglobulin Ab (Lab Code 1802105), rheumatoid factor (Lab Code 5560195), antinuclear Ab (Lab Code 5560214) (Homma, Sagawa et al. 2006); human anti-human (anti idiotypic) Ab ([name] Lab), erythrocyte sedimentation rate (Lab Code 2000860), thyroid-stimulating hormone (Lab Code 1802085), ACTH (Lab Code 1800020), cortisol (Lab Code 1802010), free T4 (Lab Code 1802081), ALT, and AST (Lab Code 1004000). Finally, if

cerebrospinal fluid becomes available, it will be checked for oligoclonal banding (Lab Code 1543440).

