Depletion or neutralization of CD25+ TRegs prior to adoptive T-cell transfer into immunocompromised mice results in a reproducible spectrum of autoimmune disease including thyroiditis, prostatitis, gastritis, orchitis, oophoritis, and insulinitis(Taguchi and Nishizuka 1987; Taguchi, Kontani et al. 1994; Seddon and Mason 1999; Seddon and Mason 1999; Bagavant, Thompson et al. 2002). However, removal of CD25+ cells alone has not proven sufficient for eliciting EAE(Fecchi, Sweeney et al. 2006).

Active immunization then in patients with GBM risks inducing an uncontrolled autoimmune response similar to EAE. Although we have not seen autoimmune manifestations with our tumor-specific EGFRvIII-targeted vaccine, our proposal to unleash secondary immune responses through IL-2R $\alpha$  blockade of TRegs may risk the induction of such deleterious autoimmune responses. Thus, this approach must be explored with particular attention to the propensity for autoimmune manifestations in treated patients.

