## 5 INVESTIGATIONAL PLAN

### 5.1 Preparation and Administration of Therapeutic Agents

#### 5.1.1 Overview

Twenty patients with newly-diagnosed EGFRvIII+ high grade glioma will undergo leukapheresis for immunologic monitoring. Only 1 dose level of daclizumab (1 mg/kg) will be assessed. The decision to dose escalate in subsequent trials will be dependent on analysis of the safety and immunologic responses obtained in this trial. Patients will be followed until death. This study will be halted if any 2 patients experience a drug-related Grade IV or irreversible Grade III toxicity. After initial leukapheresis, all patients will then receive RT and concurrent TMZ at a standard targeted dose of 75 mg/m^2/d. Patients with progressive disease during radiation, dependent on steroid supplements above physiologic levels at time of vaccination, unable to tolerate TMZ or whose PBLs fail to meet release criteria will be replaced, but no more than 40 patients will be enrolled overall. Remaining patients will then receive the initial cycle of TMZ at a targeted dose of 100mg/m^2/d for 21 days 3 ± 1 weeks after completing RT and will be independently randomized to receive daclizumab versus saline simultaneous with vaccine #1. An additional cohort of 6 patients (cohort #2) will receive serial administrations of daclizumab during vaccine # 1, vaccine # 3, and during the recovery from each TMZ cycle for the first 3 cycles at the same dose. Vaccines will be given intradermally and divided equally to both inguinal regions. The calculated dosage of daclizumab will be administered in a 50 mL of sterile 0.9% sodium chloride solution via a peripheral or central vein over a 15 minute period. Vaccine #2 and #3 will occur at 2 week intervals. Patients will then be treated monthly with TMZ cycles for a total of 6 cycles after RT. TMZ will be given on days 1-21 of a 28 day cycle. While standard dose 21-day TMZ treatment at 100 mg/m^2/day is recommended, the TMZ regimen may be adjusted at the discretion of the treating neuro-oncologist. Vaccine will always be given on day 21 ± 2 of each 28 day TMZ cycle. Subsequent vaccines will be given on day 21 ± 2 of each of the 5 remaining TMZ cycles. Cohort #2 will receive subsequent vaccinations along with daclizumab (1 mg/Kg) on day 21± 2 for first 3 cycles. Vaccines will then continue monthly until progression. An additional leukapheresis will be required for any patients who have a positive DTH skin test for PEPvIII for immunologic monitoring. Patients will be imaged after vaccine #4 and then bimonthly without receiving any other prescribed antitumor therapy until progression. Blood work for immunologic monitoring will be drawn before vaccine #1 and then monthly after vaccine #3. Blood work for sub-clinical autoimmunity will be drawn before vaccine #1 and every 4 months after vaccine #3. As part of standard care for these patients, upon tumor progression, participants may undergo stereotactic biopsy or resection. As this is not a research procedure consent will be obtained separately. However, if tissue is obtained, it will be used to confirm tumor progression histologically and to assess immunologic cell infiltration and EGFRvIII antigen escape at the tumor site.

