### **6.2.4 During and After Immunizations**

- Clinical evaluations with each vaccine or leukapheresis will include a general physical, neurologic, and ophthalmologic examination, KPS, and MMSE.
- Radiographic evaluations consisting of a contrast enhanced brain CT or MRI scan will be obtained every 8  $\pm$  4 weeks.
- Blood will be obtained for T4/T8 ratio (Lab Code 2500202), ABC (Lab Code 2010200) with manual differential (Lab Code 2000640), serum for PEPvIII-KLH ELISA ([name] Lab), and 10 yellow ACD (9 mL), 3 red (9 mL), and 1 purple (3 mL) tubes for Immunologic Monitoring *prior* to vaccination #1 and with each vaccination after vaccination #3. Blood will also be obtained for

sub-clinical autoimmunity prior to vaccine # 1 and every 4 months after vaccine # 3. Estimated volume of blood for these tests is 120 cc.

- During TMZ cycles, ABC (Lab Code 2010200) with manual differential (Lab Code 2000640) will be monitored at the time of vaccination (day  $21 \pm 2$ ) and before the next TMZ dosing of each 4 week cycle.
- DTH testing will occur with the fourth vaccination (SOP-JHS-HDC-CL-014 “Delayed Type Hypersensitivity Testing Procedure”). Results will be read and recorded on the appropriate form (FORM-JHS-HDC-CL-014C “Delayed Type Hypersensitivity Testing Form”)  $48 \pm 24$  hours later. An additional leukapheresis will be required for any patients who have a positive DTH skin test for PEPvIII for immunologic monitoring.

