| Immunization #4 (even) (Daclizumab cohort#2)  | Day 21 ± 2 of cycle           |                                                             | X                                                                     | X                 | X                                                                                                           | X                 | X                          |                                          |
| Immunization #5 (odd)                                      | Day 21 ± 2 of cycle           |                                                             | X                                                                     |                   | X                                                                                                           |                   | X                          |                                          |
| EGFRvIII +DTH                                              | +DTH                          |                                                             | X                                                                     |                   | X                                                                                                           |                   | X                          | X                                        |
| Progression                                                |                               |                                                             | X                                                                     | X                 | X                                                                                                           | X                 | X                          |                                          |

 MRI every 8 ± 4 weeks.

 10 Yellow top ACD (9 mL each) and 3 Red top (9 mL each) - all **prior** to vaccine except prior to vaccines #2 and #3 where only 4 Yellow top ACD (9 mL each) and 3 Red top (9 mL each) will be obtained . With vaccine #4, blood work for immunological monitoring will occur monthly before each vaccine. Blood work for autoimmunity monitoring will be obtained prior to vaccine # 1 and every 4 months after vaccine # 3.

 Should be read 48-72 hours after placement

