 All ABC should be obtained with manual differential counts. ABC should always be obtained with T4/T8 counts. These should be obtained at least weekly during concurrent external beam radiation and temozolomide, immediately before and within 1h after ALT, and then subsequently on day of vaccine and immediately prior to next temozolomide cycle.

 Comprehensive Metabolic Panel (CMP)

 Obtained BEFORE each leukapheresis only. B-HCG only required for females.

 MRI here is just post-operative eligibility MRI

 Post-radiation MRI will be done a minimum of 10 days after completing radiation therapy.

 Cohort 2 will receive daclizumab at same dose with vaccine # 1, # 3, and on day 21 ± 2 for 3 TMZ cycles.

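### No laboratory autoimmunity panel is scheduled for about 4.6 to 4.9 months after the first daclizumab dose, which in cohort 2 is, on the plain reading, after all planned doses

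*Protocol*

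**What the plan says.** The synopsis and sections 5.1.1, 6.1.1, 6.2.4 and 8.11 give one schedule for the autoimmunity panel. Section 8.11 puts it this way: "Patients will also be assessed before vaccine #1 and every 4 months after vaccine # 3 by a panel" of laboratory tests. Footnote 21 of the study flow sheet agrees: "Blood work for autoimmunity monitoring will be obtained prior to vaccine # 1 and every 4 months after vaccine # 3".

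The panel holds thyroglobulin antibody, rheumatoid factor, antinuclear antibody, anti-idiotypic antibody, sedimentation rate, TSH, free T4, ACTH, cortisol, ALT and AST. Section 8.11 lists hepatitis and hypophysitis among the commonest autoimmune manifestations in related trials.

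On dosing, section 5.1.1 says that cohort 1 patients "will be independently randomized to receive daclizumab versus saline simultaneous with vaccine #1", and that "Vaccine #2 and #3 will occur at 2 week intervals". Flow-sheet footnote 28 adds: "Cohort 2 will receive daclizumab at same dose with vaccine # 1, # 3, and on day 21" (± 2) for three TMZ cycles. Section 10.1 counts five daclizumab administrations in cohort 2.

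Section 3.6 concludes that "this approach must be explored with particular attention to the propensity for autoimmune manifestations in treated patients". Section 2.2.2 makes immunologic or clinical autoimmunity a secondary objective, and section 8.11.1 compares the arms on the proportion of patients with any positive panel test.

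**The concern.** The protocol treats autoimmunity as a real hazard of blocking regulatory T-cells and plans a formal between-arm comparison of it. Yet between the pre-treatment sample and a point nearly five months after the first dose, no panel is scheduled. In cohort 1, an enzyme or hormone change that appeared after the single dose and then resolved would not enter the section 8.11.1 comparison. In cohort 2, the repeat-dose group, the first panel after treatment starts would come only once dosing had ended.

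No other scheduled test fills the gap. The flow-sheet column for the metabolic panel and β-HCG is marked only at the initial leukapheresis and at the positive-DTH visit, and its footnote reads "Obtained BEFORE each leukapheresis only". Ordinary vaccine visits carry the blood count and T4/T8. So a patient without a positive DTH test has no scheduled liver, thyroid or adrenal test in this interval.

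**Working it through.** **Inputs**
- Vaccine #1 and first daclizumab dose: day 21 ± 2 (flow sheet).
- Vaccine #3: day 49 ± 7 (flow sheet). Section 5.2.1 instead spaces the first three vaccines 2 ± 1 weeks apart.
- Four months: 112 days (16 weeks) or 122 days (calendar months). The protocol does not say which, so both are shown.
- TMZ cycles of 28 days, vaccine on day 21 ± 2 of each.
- Delay to the second TMZ cycle: 1 to 3 weeks (section 3.15.2). Counting it from day 28 is my assumption, and puts the start of cycle 2 at day 35 to 49.

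**Number of doses in cohort 2.** Vaccine #1 + vaccine #3 + three cycles = 5, which reproduces the figure in section 10.1.

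**First panel after dosing** = day of vaccine #3 + 4 months.
- 49 + 112 = day 161, and 161 − 21 = 140 days; 140 / 30.44 = 4.6 months.
- 49 + 122 = day 171, and 171 − 21 = 150 days; 150 / 30.44 = 4.9 months.

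**Allowing for windows**
- Flow sheet: shortest (42 + 112) − 23 = 131 days, longest (56 + 122) − 19 = 159 days.
- 2 ± 1 week spacing: vaccine #3 is 14 to 42 days after vaccine #1, giving 14 + 112 = 126 to 42 + 122 = 164 days.
- Overall 126 to 164 days, or 4.1 to 5.4 months.

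**Cohort 2 dose days** = start of cycle 2 + 21, + 49 and + 77 (a one-day difference in counting convention is immaterial).

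| Cycle 2 starts | Dose days | Last dose to panel |
|---|---|---|
| Day 35 | 21, 49, 56, 84, 112 | 49 to 59 days |
| Day 49 | 21, 49, 70, 98, 126 | 35 to 45 days |

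All five doses precede the panel. For the fifth to fall on or after the panel day, cycle 2 would have to start more than 34 days after vaccine #3 (16-week count) or 44 days (calendar count).

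**Other readings of the dosing text**
- If the initial TMZ cycle is one of the first three, the vaccine #1 dose is counted twice and there are four doses, all still before the panel.
- The flow-sheet row for immunization #4 is labelled as covering even-numbered vaccines and carries the cohort 2 daclizumab note. If that meant vaccines #4, #6 and #8, the last dose would fall on day 35 + 133 = 168 to 49 + 133 = 182, near or after the panel. The wording elsewhere, three consecutive cycles, does not support this.

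**Flow sheet against footnote 21.** One column combines EGFRvIII PCR and ELISA with blood for autoimmunity and immunologic monitoring. After vaccine #1 it is marked at #4, #5, positive DTH and progression. On its face that would bring the autoimmunity draw forward to vaccine #4. Footnote 21 restricts it to the four-monthly schedule, in agreement with the text.

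**The case against.** The strongest reply is that autoimmunity is being watched throughout. Section 6.2.4 requires physical, neurologic and ophthalmologic examination, KPS and MMSE with each vaccine, and imaging every 8 ± 4 weeks. Section 5.4 captures any clinical or laboratory abnormality as an adverse event. Section 3.6, from which the call for particular attention comes, is about a reaction resembling autoimmune encephalomyelitis, for which the neurologic examination is far more relevant than ALT or TSH. This stands. A reader might infer that the main named risk goes unmeasured during exposure, but the documents do not support that.

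Three other tempting inferences also fail.
- That no autoimmunity information can reach a DLT decision: sections 5.3.1 and 5.3.2 base DLTs on toxicity grade, neurologic change and life-threatening events, not on the panel.
- That the panel misses the period of drug effect: section 3.13 gives depletion in monkeys of more than 4 weeks. That is a lower bound, it measures cell counts, and it cannot show a miss.
- That a calculable share of patients will progress before the panel: the median times to progression in section 3.4.3 carry no stated time origin there, and cannot simply be run from vaccine #1.

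It can also be said that section 9.2.5 describes the vaccine's autoimmune risk as delayed, that analyses beyond the primary endpoint are exploratory, and that sampling frequency is a design choice. These points lower the severity. They do not explain why a screen intended for sub-clinical disease has no time point during dosing.

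**Conclusion.** The point holds as a gap in laboratory screening, not as an absence of safety monitoring. No autoimmunity panel is scheduled from the first daclizumab dose until about 4.6 to 4.9 months later (4.1 to 5.4 with windows). In cohort 2 this first panel follows all planned doses: five on the plain reading, four if the initial cycle counts among the three. The timing relative to the last dose becomes uncertain only if the even-numbered label on the flow sheet governs dosing.

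The conclusion assumes that the four-month count starts at vaccine #3, that footnote 21 governs the combined blood column, and that cycle 2 starts within about 34 to 44 days of vaccine #3. No stated figure is wrong and the primary endpoint is untouched. This is an inexpensive improvement to a named secondary objective rather than a fault that undermines the trial.

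**What to change.** In sections 6.1.1, 6.2.4 and 8.11 and in flow-sheet footnote 21 (with the synopsis and 5.1.1 brought into line):
- Add the existing panel at vaccine #4, at the same time point in both randomised arms, and then continue every 4 months. Section 6.2.4 already draws monitoring blood "with each vaccination after vaccination #3".
- In cohort 2, also run it on the pre-vaccine blood at the daclizumab visits from vaccine #3. Footnote 21 already describes a smaller draw before vaccine #3.
- Reconcile the flow-sheet blood column with footnote 21, including whether a panel is due at progression. Reconcile the even-numbered label with the dosing text.

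This asks only for measurement. It proposes no rule linking a panel result to dosing.

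No new visit or procedure is needed. The cost is a few tubes and laboratory panels, plus more incidental abnormal values. The latter matters because section 8.11.1 calls a patient positive on any single abnormal or two-fold changed test, so extra panels raise the positive rate in both arms. Identical timing keeps the comparison fair, and 8.11.1 should say which time points enter the table.
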